### Components of the ERAS protocol

2.9

All participants in the two groups will receive perioperative care in accordance with a standardized ERAS protocol. A systematic review of colonic surgery recommended 17 vital elements of the ERAS protocol,^[31]^ components of our ERAS protocol met 14 of it (Table 1). For experimental group, acupuncture will act as additional components of ERAS.

**Table 1 T1:**
[figure not shown]
Components of an enhanced recovery program.

### Intervention

2.10

The treatment strategy of this study will be collectively formulated by experienced acupuncturists, surgeons and anesthesiologists. After laparoscopy, all the subjects will be fasted and in supine position without pillow, the intervention is going to be conducted once 30 min after surgery. The experimental group will receive the treatment of sterile disposable stainless-steel needles (*Huatuo* medical instruments Co. Ltd., Suzhou, China; 0.3 mm × 40 mm/0.3 mm × 25 mm). Acupoints will be located abiding by the World Health Organization Standard Acupuncture Point Locations in the Western Pacific Region.^[32]^ The fixed prescription includes *Hegu* (LI4), *Neiguan* (PC6), *Zusanli* (ST36), *Gongsun* (SP4), lateral line 2 of forehead (MS3), lateral line 3 of forehead (MS4), and middle line of vertex (MS5) (Fig. 3), all acupoints will be bilaterally selected except for middle line of vertex (MS5). The acupuncture needles will be inserted into acupoints after the routine sterilization; subsequently, it will be evenly lifted, inserted and then twisted to *Deqi* after reaching the standard depth; the operation of each acupoint will take 30 s. The needles will be maintained on the trunk and limbs for 30 min and on the head for 6 h after *Deqi*. Acupuncture will be performed by two acupuncturists registered in China and with over 3 years of clinical experience. They will receive the relevant training before the experiment, the training courses covered acupoint positioning, acupuncture operation skills and communication skills. The control group will be intervened by professional surgical nurses, the treatment will be intravenous injection of granisetron with 3 mg/3 mL (drug approval No. H20030161, Sichuan Taiji Pharmaceutical Co., Ltd).

**Figure 3 F3:**
[figure not shown]
The acupoints location of the fixed acupuncture prescription.

### Outcome indicators

2.11

#### Baseline data

2.11.1

The following baseline data will be recorded by the established personal information questionnaire, namely, demographic characteristics (e.g., gender, age, height, and weight), general clinical conditions (e.g., operation time, bleeding volume, anesthesia time, and intraoperative infusion volume), as well as basic vital signs (e.g., heart rate, blood oxygen, blood pressure, and respiration).

#### Primary outcome

2.11.2

Time to first flatus: the researcher will inform the subjects and their families to help record the interval between the time of subjects returning to the ward after the operation to the time of first flatus after operation.

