### Participants

2.2

All subjects will be diagnosed by two surgical experts and one anesthesiologist in accordance with the inclusion and exclusion criteria. The potential participants meeting all the inclusion criteria and match none of the exclusion criteria should communicate with the research assistant about the study face to face. The research assistant will conduct a series of disease assessment and safety assessment to eligible patients interested in the study. After signing the informed consent, subjects will be randomly split into two groups and received different treatment.

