### Inclusion criteria

2.4

Subjects will be included if meeting all the following criteria of the study:

1.the age between 18 and 70 years;2.the operation type is laparoscopic cholecystectomy, and the anesthesia type is general anesthesia, complying with the I to II classification standard of American Society of anesthesiologists;3.the intravenous analgesia pump will be employed postoperatively;4.the operation time is 2 ± 1. 0 h;5.having not undergone any other clinical trials during this study;6.without any cognitive impairment, aphasia, mental disorder, and other communication barriers;7.having participated in the trial and sign the informed consent voluntarily.

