### Randomization, allocation concealment

2.7

SPSS 25.0 will be employed to generate the random number. A specially appointed researcher will be responsible for random grouping to reduce selection bias and eliminate confounding factors. Subjects will be randomly classified into the experimental group, and the control group in the proportion of 1:1, each group will cover 90 participants. The recruiters will obtain the sequence number from the researcher responsible for assigning when eligible subjects get recruited in the trial. To further reduce the bias and prevent communication, subjects from the two groups will receive treatment in separate rooms.

To prevent researchers’ prejudice from confusing the results, the sealed envelope method will be employed to blind randomization. The distribution sequence number of subjects will be placed in the sealed and opaque envelope, so the recruiters and evaluators cannot know the allocations. To ensure strict confidentiality, the envelope will be not transparent even under strong light. To avoid confusion, the subject's name and birthdates will be written on the outside of the envelope with carbon paper. The recording of the information regarding the sealed envelope and the subject's details will be made by a video, and a copy of the outer label of the sealed letter will be attached to the group distribution card in the envelope. Afterwards, the video will be checked by another researcher to ensure that the envelopes are sealed. The whole process of opening the envelopes will be also recorded by the video as well.

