#### Secondary outcome

2.11.3

1.Time to first defecation: Researchers will inform the subjects and their families to assist in recording the interval between the time of subjects returning to the ward after the operation to the time of first defecation after operation.2.Abdominal pain: The Visual Analog Scale (VAS, Fig. 4) will be adopted to assess the degree of postoperative abdominal pain of subjects,^[27]^ which is to be recorded by researchers at t_1_ to t_5_.3.Dosage of analgesia pump: Considering that the use of analgesia pump will affect the degree of abdominal pain,^[33]^ therefore, the dosage of analgesia pump used by participants after operation will be recorded by researchers at t_1_ to t_5_.4.Abdominal distention: Likert scale (see Table 2) will be adopted to assess the degree of abdominal distention^[30,34]^ and recorded by researchers at t_1_ to t_5_.5.Nausea: The VAS scale will be employed to assess the degree of nausea^[27]^ and recorded by researchers at t_1_ to t_5_.6.Vomiting: The subjects and their families will help record the times of vomiting at t_1_ to t_5_.7.Gastrointestinal hormones: Blood samples will be taken 8 h before operation, 30 min after operation, and 24 h after operation to detect the level of gastrointestinal hormones. Enzyme-linked immunosorbent assay will be used to detect the levels of serum gastrin, motilin, ghrelin, 5-HT in the two groups. Three milliliters of blood will be harvested from the vein in the fasting state. The blood samples will be kept at ambient temperature for 30 min and then centrifuged at 3500 rpm for 10 min; the serum will be stored in a refrigerator at −70°C for testing. Serum samples will be collected by clinical centers, and relevant tests will be performed by Chengdu Lilai Biotechnology Co., Ltd.8.Psychological status: The Hospital Anxiety and Depression Scale (HADS) will be adopted to assess the psychological status of the subjects at t_0_ and t_6_.^[35]^ HADS has two subscales of anxiety and depression. There will be seven problems for anxiety and depression respectively. The anxiety and depression are expressed by the score of 0 to 7 points (no symptoms), 8 to 10 points (suspicious symptoms), 11 to 21 points (obvious symptoms). The first evaluation will be conducted 8 h before the operation, and the second one will be conducted on the day of discharge.

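### Time to first flatus and first defecation start at ward return, whose order relative to treatment is not stated, so an arm-dependent clock start is not ruled out

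*Protocol article*

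**What the plan says.** Under Primary outcome, the protocol article measures "the interval between the time of subjects returning to the ward after the operation to the time of first flatus after operation". Item 1 under Secondary outcome uses the same start: "the interval between the time of subjects returning to the ward after the operation to the time of first defecation after operation". In both cases subjects and their families help to record the interval.

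The rest of the schedule is anchored to surgery:
- **Treatment (Intervention):** for both arms, "the intervention is going to be conducted once 30 min after surgery".
- **Assessment windows (Figure 2 legend):** t1 to t5 are hours after surgery.
- **Blood samples (Secondary outcome, item 7):** the two post-operative samples are taken 30 min and 24 h after operation.

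The two treatments take very different lengths of time. For acupuncture, "the operation of each acupoint will take 30 s", and "The needles will be maintained on the trunk and limbs for 30 min and on the head for 6 h after" needle sensation is obtained. Controls receive an intravenous injection from surgical nurses. Under Randomization, allocation concealment, "subjects from the two groups will receive treatment in separate rooms"; the article does not say whether those rooms are on the ward. Under Blinding, subjects and acupuncturists are acknowledged to be unblinded.

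**The concern.** The start of a time-to-event measurement should be a point that allocation cannot move. Return to the ward is a logistical event. It occurs around the time of treatment, and treatment begins at a fixed 30 min after surgery. Nothing in the article requires ward return to come before treatment or to be independent of arm.

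If acupuncture patients reach the ward later because their session takes longer, the delay is subtracted from their recorded time to flatus. The difference then favours acupuncture without any effect on the bowel. The blinded evaluator gives no protection, because the shift lies in when the clock starts and not in how the event is judged. At stake are the only primary outcome and one secondary outcome.

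**Working it through.** **Inputs**
- Target difference 4 h, pilot SDs 2.21 h and 3.53 h, two-sided α = 0.05 (Sample size calculation).
- 90 per group (Trial design).
- 30 s per point, 30 min body-needle retention, 6 h head-needle retention (Intervention).
- Assumption, not in the document: the delay *b* in ward return, acupuncture minus control. The range considered is 0 to 6 h.

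**Step 1. Which SD to use.** The plan gives no figure for the clock start, but its sample size bears on the choice of SD. Its formula gives n = (1.96 + 0.84)² × (2.21² + 3.53²) / 4² = 7.84 × 17.345 / 16 = 8.5, so 9 per group, against the stated 78. Obtaining 78 with a 4 h difference needs a common SD of 4 / (2.8 × √(2/78)) = 8.92 h. That mismatch is a separate matter. It is used here only to set two SD scenarios: the pilot SDs and about 8.9 h.

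**Step 2. Length of the body-needle session.** Six points are needled on both sides (LI4, PC6, ST36, SP4, MS3, MS4), which makes 12, and MS5 makes 13. Needling takes 13 × 0.5 = 6.5 min. With retention the session is 36.5 min = 0.61 h. Retention alone is 0.5 h. As shares of the 4 h target: 0.5/4 = 12.5% and 0.61/4 = 15%.

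**Step 3. Effect of a shifted start.** If the acupuncture clock starts *b* hours later and there is no true effect, the expected recorded difference is *b* in favour of acupuncture. The two-sided rejection probability is Φ(b/SE − 1.96) + Φ(−b/SE − 1.96).
- Pilot SDs: SE = √(17.345/90) = 0.439 h.
- SD 8.92 h: SE = 8.92 × √(2/90) = 1.33 h.

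| Assumed shift *b* | Share of 4 h | Pilot SDs | SD about 8.9 h |
|---|---|---|---|
| 0 | 0% | 5% | 5% |
| 0.25 h | 6% | 9% | 5% |
| 0.5 h | 12.5% | 21% | 7% |
| 0.61 h | 15% | 28% | 7% |
| 1 h | 25% | 63% | 12% |
| 2 h | 50% | 99.5% | 32% |

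A 6 h shift, the full head-needle time, would exceed the 4 h target by itself. The article does not suggest that patients are kept off the ward that long.

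**Step 4. What the document settles about *b*.** It settles nothing. Treatment is at the same time point in both arms, and the rooms are separate but not located. On randomisation it says only: "After signing the informed consent, subjects will be randomly split into two groups and received different treatment". One eligibility item, "the operation time is 2 ± 1. 0 h", is known only after surgery, but the position of randomisation relative to ward return is not given.

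**The case against.** The strongest reply is that bias requires treatment to come before ward return, and no text says so. Treatment on the ward fits the description at least as well: surgical nurses treat the controls, head needles stay in for 6 h, and separate rooms are a measure against communication between groups that need not be off the ward. Where patients are treated is also an operational detail that an article may leave to the full protocol. All of this stands, and it is why the shift is given as a range that includes zero. What remains is the choice of origin, which the article does state.

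The 36.5 min figure is also one scenario: patients would have to wait for the body needles and then be moved with the head needles in place. That is correct, and the document favours no value in the range.

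A reader might infer three stronger points that the document does not support:
- **The endpoint is certainly biased towards acupuncture.** Direction and size both depend on the unstated order of events.
- **The three hospitals become non-comparable.** Differences in recovery-room stay between hospitals that affect both arms alike do not bias the randomised contrast. They add noise at most, and the pilot SDs may already contain some of it.
- **The origin is definitely a post-randomisation event.** This is plausible but not stated.

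Finally, families can observe ward return but not the end of surgery. That is a real practical advantage of the present definition, and the change has to allow for it.

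**Conclusion.** The point holds as an avoidable weakness in the endpoint definition, not as a demonstrated bias. Both bowel outcomes use a different origin from treatment and the other assessments, and nothing stated keeps that origin independent of arm.

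The false-positive rate stays at 5% if patients are on the ward before treatment. If only the body-needle session delays acupuncture patients, it is about 21 to 28% with the pilot SDs, or about 7% with the SD implied by 78 per group. These figures assume no true effect, 90 analysed per group, a normal approximation and the same delay for every acupuncture patient. A shift of 0.5 to 0.6 h could help a test reach significance. It could not by itself produce the 4 h target or the pilot difference of 26.14 − 16.31 = 9.83 h. The change is worth making because it removes the risk wherever treatment is given, at little cost.

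**What to change.** - Define time to first flatus and time to first defecation from the end-of-surgery clock time, consistent with the t1 to t5 windows.
- Have staff enter that clock time on the CRF. The operation time listed under Baseline data is a duration and does not supply it. Staff must already know the end of surgery in order to treat at 30 min.
- Also record the clock times of ward return and of each event. Subjects and families can go on noting when the event occurs.
- Report ward-return time, measured from end of surgery, by arm, so that any shift is visible.
- Keep the ward-return definition as a sensitivity analysis.

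The cost is a change of wording and a few CRF time fields, with an origin that families cannot observe and staff must supply. The sample size does not change.

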#### Secondary outcome

2.11.3

1.Time to first defecation: Researchers will inform the subjects and their families to assist in recording the interval between the time of subjects returning to the ward after the operation to the time of first defecation after operation.2.Abdominal pain: The Visual Analog Scale (VAS, Fig. 4) will be adopted to assess the degree of postoperative abdominal pain of subjects,^[27]^ which is to be recorded by researchers at t_1_ to t_5_.3.Dosage of analgesia pump: Considering that the use of analgesia pump will affect the degree of abdominal pain,^[33]^ therefore, the dosage of analgesia pump used by participants after operation will be recorded by researchers at t_1_ to t_5_.4.Abdominal distention: Likert scale (see Table 2) will be adopted to assess the degree of abdominal distention^[30,34]^ and recorded by researchers at t_1_ to t_5_.5.Nausea: The VAS scale will be employed to assess the degree of nausea^[27]^ and recorded by researchers at t_1_ to t_5_.6.Vomiting: The subjects and their families will help record the times of vomiting at t_1_ to t_5_.7.Gastrointestinal hormones: Blood samples will be taken 8 h before operation, 30 min after operation, and 24 h after operation to detect the level of gastrointestinal hormones. Enzyme-linked immunosorbent assay will be used to detect the levels of serum gastrin, motilin, ghrelin, 5-HT in the two groups. Three milliliters of blood will be harvested from the vein in the fasting state. The blood samples will be kept at ambient temperature for 30 min and then centrifuged at 3500 rpm for 10 min; the serum will be stored in a refrigerator at −70°C for testing. Serum samples will be collected by clinical centers, and relevant tests will be performed by Chengdu Lilai Biotechnology Co., Ltd.8.Psychological status: The Hospital Anxiety and Depression Scale (HADS) will be adopted to assess the psychological status of the subjects at t_0_ and t_6_.^[35]^ HADS has two subscales of anxiety and depression. There will be seven problems for anxiety and depression respectively. The anxiety and depression are expressed by the score of 0 to 7 points (no symptoms), 8 to 10 points (suspicious symptoms), 11 to 21 points (obvious symptoms). The first evaluation will be conducted 8 h before the operation, and the second one will be conducted on the day of discharge.

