## Abstract

**Background::**

Postoperative gastrointestinal dysfunction (PGD) refers to one of the common postoperative complications. Acupuncture can facilitate the recovery of PGD, whereas no therapeutic schedule of acupuncture has been internationally recognized for treating PGD. In the present study, a scientific trial protocol has been proposed to verify the feasibility of acupuncture in treating gastrointestinal dysfunction after laparoscopic cholecystectomy under general anesthesia. We conduct this protocol to investigate whether acupuncture recovery gastrointestinal dysfunction by influencing the expression of gastrointestinal hormone.

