
Some systematic reviews have also verified the feasibility of acupuncture for PGD and have drawn a positive conclusion.^[22,23]^ For the defects of research quality, statistics and research methods, the clinical results should be interpreted rigorously, and their scientific basis remain insufficient.^[24]^ Scalp acupuncture is a part of acupuncture therapy to treat diseases by stimulating specific location of the head area, showing a considerable effect on numerous diseases resulting from the brain.^[25]^ The acupuncture prescriptions for PGD primarily involve the points located in trunk and limbs.^[26]^ In the present clinical trial, the acupoints in the head area will be chosen in accordance with brain-gut axis theory, which is a novel exploration and attempt to apply acupuncture for PGD. By referencing to the design of similar studies,^[27]^ 18 patients having undergone laparoscopic surgery were pre-tested strictly following the evaluation and treatment process of this study. These subjects were randomly classified to “experimental group” (acupuncture) and “control group” (granisetron); the experimental group (16.31 ± 2.21 h) had a shorter average time to first flatus than the control group (26.14 ± 3.53 h). According to the preliminary results, acupuncture can effectively relieve gastrointestinal dysfunction after laparoscopic cholecystectomy.

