#### Statistical analysis

2.15.2

1.Analysis procedures sample distribution: The number of dropouts and the rate will be described and analyzed for each data set, and the reasons for any dropouts are elucidated.2.Balance comparison: The subjects’ general data will be compared to assess the comparability of the two groups.3.Efficacy analysis: The subjects’ time to first flatus will be used as the primary outcome measure to assess the efficacy and safety of acupuncture in treating PGD. The means (χ) and standard (SD) deviations will be calculated to express the outcome measure, and the experimental and control groups will be statistically compared by two independent-sample *t* tests. Eight secondary outcomes will be applied to assess the efficacy of the acupuncture. Seven of these—namely, time to first defecation, abdominal pain, dosages of analgesia pump, abdominal distention, nausea, vomiting, and gastrointestinal hormones will be described usinḡχ± SD deviation and statistically compared between groups by Repeated Measures Analysis of Variance (RMANOVA). The statistical analysis of time to first defecation will be identical to that of time to first flatus. However, before performing RMANOVA, a sphericity test will be performed to determine whether the data are suitable for analysis by RMANOVA. If the data do not conform to the conditions of sphericity condition, the degree of freedom will be corrected using factor ε before the RMANOVA is performed. The categorical measure of psychological status will be analyzed using either the rank-sum test or Spearman's rank correlation.4.Safety analysis: In accordance with the definition of adverse events, specific adverse events, their severity level, causes, and explanations will be listed. The number of adverse events, and the incidence of adverse event will be statistically described. If inter group comparison is required, the χ^2^ test or Fisher's exact test will be performed.5.Methods of statistical analysis: An independent statistician analyzed the outcome data in accordance with the principle of intention-to-treat (ITT), that is, all subjects recruited in the group will be covered. The analysis of efficacy and safety indicators will be conducted following the principle of per-protocol (PP), that is, all subjects who completed the whole trial process without major protocol violations will be included. All statistical analysis complied with ITT population, and the results of ITT analysis will be compared with PP analysis to assess the sensitivity. All missing data will be analyzed using the last observation carried forward (LOCF) interpolation method. The qualitative data will be tested for normality, according to which independent *t* test or Mann–Whitney *U* test will be performed for groups comparison. Qualitative variables will be presented by the statistical description of χ ± SD of the normal distribution data, whereas qualitative variables will be recorded as the number of cases in each category. If the quantitative variables constitute repeated measures data, RMANOVA will be adopted for comparison, and the sphericity test will be performed to ascertain the applicability of, as well as to correct the data. The categorical variables will be represented by numbers (percentages) by χ^2^ test or Fisher's exact test *P* < .05 will be considered statistically significant on both sides in all the statistical tests. SPSS 25.0 software (SPSS, SPSS Inc, Chicago, IL) will be adopted for data statistical analysis.

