Given the theoretical research of acupuncture and long-term clinical experience, this study hypothesizes that acupuncture may promote the recovery of gastrointestinal dysfunction after laparoscopic cholecystectomy under general anesthesia by changing the level of gastrointestinal hormones. A systematic review^[35]^ revealed that the time to first flatus after operation is of high clinical implication in the recovery of gastrointestinal motility.^[39]^ In most clinical trials regarding PGD, the time to first flatus is considered as the primary result, so it acts as the main outcome index here. PGD can cause emotional impact on patient, so the anxiety and depression of the subjects act as the secondary observation indexes as well.^[40]^ In the inclusion criteria of this study, subjects aged from 18 to 70 will be selected to cover as wide a range as possible. In the meantime, exclusion of participants taking gastrointestinal motility related drugs is critical for accurate clinical results. During the study, patients will be allowed to use rescue drugs when having intolerable symptoms; this strategy reflects the clinical practice in the real world and meets the moral obligation.

This study has some limitations. To be specific, the drug control group was designed, instead of the placebo sham acupuncture control group. In the previous experiment, we found that even intradermal acupuncture or transcutaneous electrical stimulation can exert physiological effects, which might be attributed by the specificity of acupoints. At present, there has been an absence of internationally recognized criterion and mature method of sham acupuncture.^[41]^ Moreover, it is difficult to blind subjects since most of Chinese patients have received acupuncture before, so the trial lacked sham acupuncture control group. In brief, this study protocol described a randomized, evaluated blinded, multi-center clinical controlled trial. The results of this study will evidence the effectiveness, safety, and feasibility of acupuncture for gastrointestinal dysfunction after laparoscopy; the aim of this study is to provide reliable reference for facilitating the clinical application of this therapy.

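### Hormones: only the 24 h sample is clearly post-treatment, the deciding RMANOVA term is not named, and one late sample cannot show that hormone change came before recovery

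*Protocol article*

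**What the plan says.** **Sampling.** Section 2.11.3, item 7: "Blood samples will be taken 8 h before operation, 30 min after operation, and 24 h after operation". Serum gastrin, motilin, ghrelin and 5-HT are measured.

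**Treatment.** Section 2.10: "the intervention is going to be conducted once 30 min after surgery". For the acupuncture group, "The needles will be maintained on the trunk and limbs for 30 min and on the head for 6 h after" the needling sensation is obtained.

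**Analysis.** Section 2.15.2, item 3, lists hormones among the outcomes "statistically compared between groups by Repeated Measures Analysis of Variance (RMANOVA". A sphericity test comes first, with an epsilon correction of the degrees of freedom if it fails. The section does not say whether the group effect or the group-by-time term decides, and it names no covariates.

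**Aim.** The Abstract (Background) sets out to learn "whether acupuncture recovery gastrointestinal dysfunction by influencing the expression of gastrointestinal hormone". The Discussion hypothesises that "acupuncture may promote the recovery of gastrointestinal dysfunction after laparoscopic cholecystectomy under general anesthesia by changing the level of gastrointestinal hormones".

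**Flatus.** In the 18-patient pilot (Introduction), "the experimental group (16.31 ± 2.21 h) had a shorter average time to first flatus than the control group (26.14 ± 3.53 h". Section 2.11.2 defines flatus time as "the interval between the time of subjects returning to the ward after the operation to the time of first flatus after operation". Section 2.15.1 plans on a 4 h reduction.

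**The concern.** There are two linked problems.

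1. **The test.** The 8 h pre-operative value cannot carry a treatment effect. The 30 min draw and the treatment share one nominal time, so at most it catches the first moments of treatment. RMANOVA counts both as outcomes alongside the 24 h value. If the comparison between groups is read as the group main effect, an effect present only at 24 h is averaged with two near-zero differences. With the term left open, the result can turn on which line of the output is reported, and the choice could be made after the results are seen.

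2. **The inference.** The stated aim is causal: recovery through hormones. No sample is scheduled between 30 min and 24 h. If more acupuncture than control patients have already passed flatus when the 24 h sample is drawn, a hormone difference may be a consequence of recovery as easily as its cause. At stake is a conclusion about mechanism that the sampling scheme cannot carry.

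**Working it through.** The protocol gives no power figure, variance or target effect for hormones, so there is no stated figure to reproduce.

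**Part 1: which sample is post-treatment**

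| Event | Time relative to operation |
|---|---|
| Sample 1 | -8 h |
| Sample 2 | +0.5 h |
| Treatment starts | +0.5 h (order relative to sample 2 not stated) |
| Head needles out | about 0.5 + 6 = 6.5 h |
| Sample 3 | +24 h |

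Only sample 3 is clearly post-treatment.

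**Part 2: power by choice of test**

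From the document: three samples, two-sided alpha 0.05, and n = 78 per group (section 2.15.1, before dropout inflation, used here only as the number analysed). Assumed: effect d = 0.5 SD at 24 h and zero at the other two times, equal variances, and a common correlation r of 0.3, 0.5 or 0.7 between samples. Power is from the noncentral F distribution.

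- Group main effect: the difference is d/3 = 0.167 SD and the variance of a three-sample mean is (1 + 2r)/3. λ = (n/2)(d/3)² / [(1 + 2r)/3], on 1 and 154 df. At r = 0.5: 39 × 0.0278 / 0.667 = 1.63.
- Group-by-time: λ = (n/2) × d² × (2/3) / (1 - r), on 2 and 308 df. At r = 0.5: 39 × 0.1667 / 0.5 = 13.0.
- ANCOVA at 24 h on both earlier values: R² = 2r²/(1 + r), λ = (n/2)d²/(1 - R²), on 1 and 152 df. At r = 0.5: R² = 0.333 and 9.75 / 0.667 = 14.6.
- ANCOVA on the pre-operative value only: λ = (n/2)d²/(1 - r²), on 1 and 153 df. At r = 0.5: 9.75 / 0.75 = 13.0.

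| Test | r = 0.3 | r = 0.5 | r = 0.7 |
|---|---|---|---|
| RMANOVA group main effect | 29% | 24% | 21% |
| RMANOVA group-by-time | 78% | 91% | 99% |
| ANCOVA, pre-operative value only | 90% | 95% | 99% |
| ANCOVA, both earlier values | 92% | 97% | 99.8% |

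An unadjusted t test at 24 h has 87% power. With all 90 per group analysed, the ranges are 24-33% (main effect), 84% to over 99% (group-by-time) and 95% to over 99% (ANCOVA on both values).

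**Part 3: flatus relative to the 24 h sample**

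Flatus is timed from return to the ward and the sample from the operation. The gap g between the two clocks is not given; 0 to 2 h is assumed. Share past flatus at the sample = Φ((24 - g - mean)/SD), by normal approximation.

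- Acupuncture, pilot: g = 0, Φ(7.69/2.21) = 99.97%; g = 2, Φ(5.69/2.21) = 99.5%.
- Acupuncture, 4 h planning effect (mean 26.14 - 4 = 22.14 h, SD 2.21): g = 0, Φ(1.86/2.21) = 80%; g = 1, 65%; g = 2, Φ(-0.14/2.21) = 47%.
- Control, pilot: g = 0, Φ(-2.14/3.53) = 27%; g = 2, Φ(-4.14/3.53) = 12%.

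At each gap, more acupuncture than control patients are past flatus: 80% or 99.97% against 27% at g = 0, and 47% or 99.5% against 12% at g = 2.

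**The case against.** **The plan's test is not shown to be diluted.** Only the group main effect shrinks. The sphericity test and epsilon correction concern within-subject terms, which suggests an analysis that includes group-by-time, and that term keeps 78-99% power. This stands: a reader might infer that the hormone test has about 25% power, but the document does not say that the main effect decides. Naming the term could also be left to a fuller document. What remains is that the article fixes RMANOVA as the method and describes it as a comparison between groups, a wording that fits the weak term at least as well as the strong one. ANCOVA on values already collected does better than either.

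**The 30 min sample may not be pre-treatment.** This stands. Its place before needling or injection is inferred from equal nominal times, so adjustment for it must be conditional on the order being stated.

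**The 24 h sample does not follow flatus in nearly all acupuncture patients.** A reader might infer this from the pilot, but it rests on 18 patients and a 9.83 h difference (26.14 - 16.31). The protocol's own 4 h planning effect gives 47-80%. The size of the imbalance is therefore uncertain. Its direction is the same at every gap considered.

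**The hormone question is not lost.** This stands in part. Whether levels differ between groups at 24 h remains testable. Flatus before the sample shows only that the measurement came later, not that the hormone change did. That uncertainty about order is why the causal wording goes too far.

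**Conclusion.** The point holds in a limited form. One of three hormone samples is clearly post-treatment, and the analysis names no deciding term and makes no covariate use of the earlier values. Under the assumed 0.5 SD effect, equal correlations of 0.3 to 0.7 and 78 per group, the unnamed choice lies between 21-29% and 78-99% power, while ANCOVA on both earlier values gives 92-99.8%. At r = 0.5, moving from group-by-time to ANCOVA gains about 6 points (91% to 97%). The larger gain is to rule out the main-effect reading and to have one adjusted 24 h difference to report.

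The mechanism wording in the Abstract and Discussion exceeds what the sampling can support, because a 24 h difference cannot show that hormone change came before recovery. The documents do not support saying that the plan's test is underpowered as such, or that nothing can be learned about hormones.

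These are secondary outcomes, but they carry the protocol's stated hypothesis, so the change is worth making.

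**What to change.** 1. In section 2.15.2, replace the RMANOVA between-group comparison for hormones with ANCOVA of each hormone at 24 h as the deciding analysis. Adjust for the pre-operative value and, provided it is drawn before treatment, the 30 min value. If that order cannot be assured, adjust for the pre-operative value alone (90-99% power under the same assumptions), since a sample taken after treatment has begun could absorb part of the effect.
2. In sections 2.10 and 2.11.3, state whether the 30 min sample is taken before needling or injection.
3. In the Abstract and Discussion, restate the aim and the planned conclusion as an effect on 24 h hormone levels, not as recovery brought about by changing hormones.

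The cost is wording only: no extra patients, samples or visits. Moving one draw to a time after treatment and before expected flatus is optional and not part of the required change. It would show temporal order at the price of an existing time point, and would still not by itself establish mediation, because hormone level is not randomised.
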